### Study objectives

We hypothesise that providing office-based physicians with comprehensive information on their patients’ treatments and diagnoses, and giving these physicians the opportunity to discuss this information with colleagues who treat the same patients, might improve care coordination and patient outcomes in the ambulatory care sector.

In Germany, physicians do not necessarily learn about the other treatments or diagnoses unless the patient tells them or asks explicitly for their records to be transferred from one doctor to another. Analysing large, merged data sets from Regional Associations of SHI Physicians (ASHIP) and large statutory health insurers allows us to follow patient pathways, including all appointments, treatments, medications and diagnoses across the health system over time. The objectives of our study are to use this information to (1) identify informal networks of physicians who treat the same patient population, (2) provide the physicians with feedback on their network and patients based on routine data and, (3) give the physicians the opportunity to meet one another in facilitated network meetings.

We will use the routine data described above to identify informal networks of physicians who provided care to the same patients with chronic diseases during a specified period. The physicians in these networks will receive feedback on selected indicators of per-physician treatment activity in their network and the care received by patients. Subsequently, the physicians will be invited to voluntary, facilitated network meetings during which they will be able to use the information provided to them to discuss the challenges of coordinating care in everyday medical practice and can jointly agree upon clinical pathways for selected indications. These networks will be compared to informal networks that did not receive additional information or invitations to meetings and that provide usual care.

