The secondary outcome will be rates of treatment provided in accordance with the relevant clinical practice guidelines. Treatment in this context will be defined as (a) the type and amount of medication prescribed by physicians in the networks, (b) whether regular follow-up visits have taken place and (c) whether the physicians follow the recommended diagnostic procedure [15–19].

Both the primary and secondary outcomes will be calculated based on the routine data described above and evaluated at baseline, at the end of the 2-year intervention period, and at 6 months and at 12 months after the end of the intervention period. The outcomes will be evaluated using an intention-to-treat approach within multi-level models [20].

Additionally, in accordance with MRC guidelines [21], we will undertake a process evaluation and a cost-effectiveness analysis. Through the latter, it will be possible to evaluate how changes in the relevant medical effects of the intervention are related to changes in its costs [22]. The analysis will take account both of additional costs from the perspective of the statutory health insurers (payer perspective) and the marginal effects of hospitalisation rates among the intervention networks compared to those among the control networks. This information will be used to discuss the potential to implement the intervention to other contexts within Germany [21].

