### Randomisation and sample size estimation

Among the networks identified in the data set described above, we will select a random sample of 100 intervention and 100 control networks. These networks will be divided into strata according to (a) the four regions covered by the Regional Associations of SHI Physicians and (b) whether they are located in an urban or rural area, as it can be assumed that the structure of the networks will differ depending on their location, which, in turn, will have an impact on the measured outcomes [23]. Within these strata, the networks will be randomised to the intervention and control groups with equal size [24]. Networks of the strata will be randomly assigned to the intervention or control group by statisticians of the Hannover Medical School using the software nQuery 7.0. The statisticians are not otherwise involved in the planning of the study design. Sequence allocation and assignment is conducted based on the network identifier (generated by the study group) without information on physician identities.

The sample size estimation based on the assumption of a 20% hospitalisation rate and a 15% reduction in ACSHs following the intervention, we thus expect a 17% ACSH rate in the intervention group. The numbers were chosen after reviewing comparable studies and analysing hospital routine data [14, 25, 26]. With a 5% significance level and a power of 80%, 2629 patients per group would be needed to show this effect (2-sided *χ*^2^ test). For cluster-randomised studies, the estimated sample size must be adjusted by the design effect, which is a function of cluster size and the intracluster correlation coefficient (ICC). Assuming an ICC of 0.015 [27] and an average of 300 patients per network yields a design effect of 5.485. This means that the estimated number of cases of an individual-randomised study has to be multiplied by 5.485. With this design effect, 28,840 patients and thus 96 networks per arm (intervention and control) will be needed.

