As described above, the intervention networks will receive feedback sheets and be invited to facilitated network meetings by the Regional Association of SHI physicians. According to Section 287 of Book V of the German Code of Social Law (§ 287 SGB V) the regulatory authorities confirmed that Regional Associations of SHI Physicians may send the feedback sheets to their members without prior written, informed consent by the office-based physicians (please see section on ‘participant consent’). Participation in the informal network meetings will, however, be voluntary. Data will be analysed using an intention-to-treat approach, with all office-based physicians who receive feedback sheets being considered in the evaluation, regardless of whether they participate in the voluntary network meetings. This approach will help avoid biased estimates due to the self-selection of physicians who are more enthusiastic about taking part in the network meetings [28]. Furthermore, we will slightly oversample the informal networks (100 instead 96) in case all physicians in an informal network formally reject the feedback sheets sent by the Regional Association of SHI physicians.

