**Fig. 3 Fig3:**
[figure not shown]
Data flow and pseudonymisation in the ACD study

The Regional Associations of SHI Physicians will use the same tool to pseudonymise the patient IDs, physician IDs and medical practice IDs. The tool uses a hash-algorithm to generate 40-digit pseudonyms. All IDs are extended by a “secret” prior to the hashing. This secures the pseudonyms against random hits when attempting re-pseudonymisation using brute force methods. The pseudonymised data are then sent via an SFTP server provided by the Central Institute for SHI Physician Care in Germany (Zi), who will combine the physician association data by regions before forwarding them to the analysts. Furthermore, to enable the data linkage, the Regional Associations of SHI Physicians will send lists (key lists) of un-pseudonymised physician IDs to the Trust Centre. With these lists, the Trust Centre can check whether physicians have been pseudonymised correctly.

The statutory health insurers will send their data via a secure data server connection to the Trust Centre. The patient data will be pseudonymised, and the physician’s office and hospital IDs will be sent un-pseudonymised. The Trust Centre uses a reversible dual technique to pseudonymise the physician data. The IDs of physicians who are part of the Regional Associations of SHI Physicians will be pseudonymised/replaced with the pseudonym from the key lists. Lastly, the pseudonymised data will be secured in a VeraCrypt container and transferred via external hard drives to the analysts. Analysts will have information on the allocation of physician pseudonyms to intervention and control networks. For the analysis, the data will be placed on a separate server and kept in a secure VeraCrypt container, accessible to the analysts only.

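### The intention-to-treat set is worded by receipt of feedback sheets, and the protocol does not say that physicians or networks rejecting the sheets stay in their allocated arm

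*Protocol article*

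**What the plan says.** The paragraph that describes who is evaluated is in the Protocol article, Randomisation and sample size estimation. It names the intention-to-treat approach and explains it as "with all office-based physicians who receive feedback sheets being considered in the evaluation, regardless of whether they participate in the voluntary network meetings". It gives avoidance of self-selection into the meetings as the reason. It then says that "we will slightly oversample the informal networks (100 instead 96) in case all physicians in an informal network formally reject the feedback sheets".

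The sheets go to one arm only. In the same section, "the intervention networks will receive feedback sheets and be invited to facilitated network meetings by the Regional Association of SHI physicians". Under Study objectives, the control condition is set out: "These networks will be compared to informal networks that did not receive additional information or invitations to meetings and that provide usual care".

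Outcomes repeats the principle without defining a set: "The outcomes will be evaluated using an intention-to-treat approach within multi-level models". The data management section adds that "Analysts will have information on the allocation of physician pseudonyms to intervention and control networks".

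**The concern.** Receiving or rejecting a sheet happens after randomisation and can happen only in intervention networks. If it decides who is evaluated, the intervention arm passes through a filter that the control arm does not.

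Physicians who formally reject feedback may differ from the rest in their patients and in how they coordinate care. Dropping them would make the arms differ for reasons other than the intervention. The paragraph guards against this problem for meeting attendance and leaves it open one step earlier, at the sheets.

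The reserve sentence points the same way. Extra networks to cover rejection are needed mainly if a rejecting network leaves the analysis. Under analysis as allocated, such a network stays in its arm and is not lost.

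**Working it through.** **1. The plan's own figures.** Inputs from Randomisation and sample size estimation: rates 20% and 17%, two-sided 5% level, 80% power, ICC 0.015, 300 patients per network.

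- Two-proportion formula with pooled variance: 2629 per group, which matches.
- Design effect: 1 + (300 − 1) × 0.015 = 5.485, which matches.
- Per arm: 2629 × 5.485 = 14,420 patients; 14,420 / 300 = 48.07 networks.
- Both arms: 2 × 14,420 = 28,840 patients; 28,840 / 300 = 96.1 networks.

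So 28,840 patients and 96 networks reproduce as totals for both arms, not per arm as labelled. That is a separate point. It matters here only because the reserve is counted from 96, and because 100 networks per arm leave ample power (step 4).

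**2. Bias if rejecters are dropped.** The document gives no rejection rate and no risk for rejecters, so both are assumed. Let q be the share of intervention patients excluded and RR their risk relative to the rest, with no true effect and an overall rate of 20%.

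Retained rate = 0.20 / (q × RR + 1 − q). Bias = 0.20 − retained rate; a positive value favours the intervention.

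The reserve of 4 in 100 suggests q = 0.04 if networks are of similar size.

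| q | RR | Retained rate | Bias (points) | Share of the planned 3 points |
|---|---|---|---|---|
| 0.04 | 1.10 | 0.20/1.004 = 19.92% | 0.08 | 3% |
| 0.04 | 1.25 | 0.20/1.010 = 19.80% | 0.20 | 7% |
| 0.04 | 0.80 | 0.20/0.992 = 20.16% | −0.16 | 5%, against the intervention |
| 0.10 | 1.25 | 0.20/1.025 = 19.51% | 0.49 | 16% |
| 0.20 | 1.25 | 0.20/1.050 = 19.05% | 0.95 | 32% |

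The last two rows apply only if rejection goes well beyond the reserve.

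**3. Effect on type I error.** With 100 networks of 300 per arm (30,000 patients), SE = √(2 × 0.20 × 0.80 × 5.485 / 30,000) = 0.00765. Type I error = Φ(−1.96 + bias/SE) + Φ(−1.96 − bias/SE).

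- Bias 0.00080: ratio 0.10, type I error 5.1%.
- Bias 0.00198: ratio 0.26, type I error 5.8%.
- Bias 0.00488 (q = 0.10): ratio 0.64, type I error 9.8%.

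**4. Power if rejecters are kept.** Suppose a share f of the intervention arm rejects, gains nothing and stays in its arm. The intervention rate becomes 0.20 − 0.03 × (1 − f). With 100 networks of 300 per arm:

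| f | Intervention rate | Power |
|---|---|---|
| 0 | 17.00% | 98.1% |
| 4% | 17.12% | 97.2% |
| 10% | 17.30% | 95.2% |
| 20% | 17.60% | 89.5% |

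Under the plan's own assumptions, power stays above 80% throughout.

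**The case against.** The strongest reply is that the sentence contrasts being sent sheets with attending meetings, and that its purpose is to keep non-attenders in. It does keep them, which is right. Sheets go out without prior written consent, so receipt should lie close to allocation. The reserve is triggered only when every physician in a network of 20 to 120 rejects, which may be rare. One physician's refusal need not remove shared patients, since allocation and the random effect are at network level. All of this stands, and it limits the likely size of the bias. It does not supply the missing statement that rejecters are analysed as allocated.

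Three stronger readings are tempting and not supported:

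- A reader might infer that the protocol excludes rejecting networks. It never says so. A reserve could also offset dilution, and it is applied to both arms: "we will select a random sample of 100 intervention and 100 control networks". Replacement of losses is the more natural reading, but it remains an inference.
- A reader might infer that control physicians, who get no sheets, fall outside the set. Study objectives, Outcomes and Statistical methods all describe a comparison of intervention with control networks, so this reading fails.
- A reader might take the exclusion of 10% or 20% of patients as the expected case. Neither figure comes from the document.

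The paragraph also refers to a section on participant consent that is not in the available text. That section may say what a formal rejection means for use of the data, so it cannot be asserted that nothing could require their removal.

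**Conclusion.** The point holds as a defect of wording in the rule that governs the primary comparison. The only description of the evaluated physicians ties them to receipt of sheets. That sits badly with the intention-to-treat label and with the paragraph's own argument about self-selection, and handling of rejecters is not stated.

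If the wording were followed, exclusion at the level of the reserve would shift the difference by about 0.08 to 0.20 points at risk ratios of 1.1 to 1.25, with type I error of at most about 5.8%. Larger distortion needs rejection beyond the reserve. The sign depends on who rejects. These figures rest on assumed rejection shares and risk ratios, no true effect, similar network sizes, and the plan's ICC and 300 patients per network.

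**What to change.** In Randomisation and sample size estimation, replace the reference to physicians receiving sheets. Define the evaluated set as all randomised networks, all physicians assigned to them at randomisation, and their eligible patients, analysed in the allocated arm whether or not sheets were received or rejected. Report the number of rejecting physicians and networks as adherence. If the reserve is kept, describe it as covering dilution and not as replacing excluded networks.

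The cost is wording. The outcomes come from routine data and the analysts know each physician pseudonym's allocation, so analysis as allocated is feasible, subject to whatever the consent section says about data use. The downside is slight dilution: at 4% rejection with no effect among rejecters, the planned 3 points become 3 × 0.96 = 2.88.

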## Data management, statistical methods and ethics

### Data management and approval by regulatory authorities

Our application to use administrative data for the ACD study was granted by the regulatory authorities of the Regional Association of SHI Physicians in North Rhine (State Ministry of Employment, Health and Social Affairs in North Rhine Westphalia, granted 2017/11/21), Westphalia Lip (State Ministry of Employment, Health and Social Affairs in North Rhine Westphalia, granted 2017/11/21), the Hamburg Senate for Health and Consumer Protection (granted 2018/02/15) and Schleswig Holstein (State Ministry of Health, Youth, Families and Seniors in Schleswig Holstein, granted 2017/09/29)), as well as by AOK Rhineland/Hamburg and AOK North West (Ministry of Employment, Health and Social Affairs in North Rhine Westphalia, granted 2017/10/24), and the Techniker Krankenkasse (Federal Office for Social Security, granted 2017/09/22). The state ministries are the responsible regulatory authorities in the states. The Techniker Krankenkasse, which provides statutory insurance on a nationwide basis, is supervised by the Federal Office for Social Security.

Following our application to the relevant regional regulatory authorities in accordance with Section 75 of Book X of the German Code of Social Law (§75 SGB X), data from the Regional Associations of SHI Physicians and the statutory health insurers will be linked within a Trust Centre. The data linkage and the pseudonymisation are shown in Fig. 3.

**Fig. 3 Fig3:**
[figure not shown]
Data flow and pseudonymisation in the ACD study

The Regional Associations of SHI Physicians will use the same tool to pseudonymise the patient IDs, physician IDs and medical practice IDs. The tool uses a hash-algorithm to generate 40-digit pseudonyms. All IDs are extended by a “secret” prior to the hashing. This secures the pseudonyms against random hits when attempting re-pseudonymisation using brute force methods. The pseudonymised data are then sent via an SFTP server provided by the Central Institute for SHI Physician Care in Germany (Zi), who will combine the physician association data by regions before forwarding them to the analysts. Furthermore, to enable the data linkage, the Regional Associations of SHI Physicians will send lists (key lists) of un-pseudonymised physician IDs to the Trust Centre. With these lists, the Trust Centre can check whether physicians have been pseudonymised correctly.

The statutory health insurers will send their data via a secure data server connection to the Trust Centre. The patient data will be pseudonymised, and the physician’s office and hospital IDs will be sent un-pseudonymised. The Trust Centre uses a reversible dual technique to pseudonymise the physician data. The IDs of physicians who are part of the Regional Associations of SHI Physicians will be pseudonymised/replaced with the pseudonym from the key lists. Lastly, the pseudonymised data will be secured in a VeraCrypt container and transferred via external hard drives to the analysts. Analysts will have information on the allocation of physician pseudonyms to intervention and control networks. For the analysis, the data will be placed on a separate server and kept in a secure VeraCrypt container, accessible to the analysts only.

The data provided by the Regional Associations of SHI Physicians encompass all patient contacts in the ambulatory care sector that are billed to the statutory health insurer except for some cross-sectoral services and services purchased through selective contracting. The data provided by the statutory health insurers encompass all patient contacts billed to participating statutory health insurers, including contacts in hospitals. The data are collected for billing purposes and are therefore routinely subject to thorough quality control by the data holder. Additional quality checks of the data will be conducted by the Trust Centre, the Central Institute for SHI Physician Care in Germany and the analysts. These quality checks will include summary statistics of variables and the systematic comparison of different data tables.

An external data monitoring committee was not established in the study due to the non-invasive character of the study with no critical safety concerns for patients or physicians. Instead, a project board was established. This board consisted of one representative of the project management, one for the scientific project partners, one for the associations of statutory health insurance physicians, and one for the health insurance funds. The board holds biannual conferences on the status of the project.

### Statistical methods

The networks will be identified in an iterative fashion. Patients shared by the office-based physicians will be arranged into a matrix that will be used to generate the network structure. This will subsequently be divided into intervention networks using the modularity optimising multilevel algorithm of the igraph package in R. The indicators for the feedback sheet will comprise the characteristics of the networks and the underlying patient population, which will be summarised using descriptive statistics. The indicators of quality of patient care will be calculated as combined indicators encompassing medication, procedures, use of services and/or (re-)admissions.

For the evaluation, we will analyse differences in the primary and secondary outcomes between the intervention and control groups. Despite randomisation, it is conceivable that the results might be affected by external factors, such as the individual disease risk of patients, itself driven by differences, for example, in demographics [29], compliance [30], socioeconomic factors [31], and the organisation of the hospital sector [32]; this will therefore be adjusted using multilevel regression models with the network as random effect.

Comprehensive sensitivity analyses of the evaluation outcomes are planned, including systematic comparisons of competing models of risk adjustment [33] and different levels of significance.

For the cost-effectiveness analyses, the cost data will be taken from the routine data provided by the three participating statutory health insurers (Techniker Krankenkasse, AOK Rhineland/Hamburg, AOK North West). We will use the German standard cost model and choose the perspective of the statutory health insurers (i.e., the payer perspective) in order to provide information for reimbursement decisions. The primary outcomes of the cost-effectiveness analyses will also be hospital admissions resulting from ambulatory-care-sensitive conditions. The incremental cost-effectiveness ratios (ICER) will be calculated using bootstrapping methods. The statistical uncertainty will be estimated using cost-effectiveness acceptability curves (CEAC).

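### The described outcome model names neither the randomisation strata nor the baseline rate of ambulatory-care-sensitive hospitalisation (ACSH); stating both as primary-model terms would give a correct and smaller standard error at almost no cost

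*Protocol article*

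**What the plan says.** All places are in the protocol article.

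- **Randomisation and sample size estimation.** Networks are grouped by the four regional physician associations and by urban or rural location. The reason given is that network structure "will differ depending on their location, which, in turn, will have an impact on the measured outcomes". Allocation respects the grouping: "Within these strata, the networks will be randomised to the intervention and control groups with equal size".
- **Outcomes.** The primary and secondary outcomes are "evaluated at baseline, at the end of the 2-year intervention period, and at 6 months and at 12 months after" the end of the intervention, by intention to treat within multi-level models. A baseline ACSH value is therefore planned from the routine data.
- **Statistical methods.** Arms are compared after adjustment for external factors. The examples given are individual disease risk (driven by demographics, compliance and socioeconomic factors) and the organisation of the hospital sector. The model is then described: "this will therefore be adjusted using multilevel regression models with the network as random effect". Sensitivity analyses will compare competing risk-adjustment models.

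No section names region, urban/rural location or the baseline ACSH rate as a model term. No section excludes them.

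**The concern.** The design singles out location as prognostic and restricts the randomisation on it. The analysis section lists other kinds of factor and does not mention this one.

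Stratified allocation balances the strata between arms, so the true sampling variance of the treatment effect no longer contains the between-stratum component. A model without the strata leaves that component in the network variance. Its standard error is then too large, its intervals too wide, and its nominal 5% test rejects less than 5% of the time under the null.

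The baseline rate raises a different issue. With a few hundred patients per network, most of the variance of a network's observed rate is between networks. If networks with high ACSH rates tend to keep them, the network's own earlier rate is likely to be one of the strongest predictors available. Leaving it out does not make the standard error wrong. It makes it larger than it need be.

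**Working it through.** **Inputs from the protocol** (Randomisation and sample size estimation)
- Rates: "assumption of a 20% hospitalisation rate and a 15% reduction in ACSHs following the intervention", giving 20% against 17%.
- Two-sided 5% level, 80% power, 2629 patients per group before clustering.
- ICC ρ = 0.015, m = 300 patients per network, 100 networks per arm.
- Up to 4 × 2 = 8 strata.

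**Assumed, because the protocol gives no figure**
- R, the share of between-network variance explained by strata: 10–30%.
- c, the correlation of network effects between baseline and follow-up: 0.7–0.9.

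**1. The plan's own figures.** The two-proportion formula with pooled variance and no continuity correction gives 2628.6, so 2629 per group. The design effect is 1 + 299 × 0.015 = 5.485. Both reproduce.

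**2. Strata left out.** Adjusting for strata lowers the design effect to (1 − ρ) + mρ(1 − R) = 0.985 + 4.5(1 − R). The unadjusted model still estimates 5.485, so its standard error is too large by the factor √(5.485 / reduced value).

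| R | Reduced design effect | Model SE / true SE | Actual type I error, 2Φ(−1.96 × ratio) |
|---|---|---|---|
| 0 | 5.485 | 1.00 | 5.0% |
| 10% | 5.035 | 1.04 | 4.1% |
| 25% | 4.360 | 1.12 | 2.8% |
| 30% | 4.135 | 1.15 | 2.4% |

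A network-level simulation (200 networks, 8 strata, 1,500 runs per setting) agrees. Without strata, type I error was 0.042–0.048 at R = 10% and about 0.03 at R = 25%. With strata in the model it was 0.048–0.059, which is 5% within simulation error.

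**3. Baseline left out.** The between-network share of the variance of a network mean is mρ / (1 + (m − 1)ρ) = 4.5 / 5.485 = 0.820. The correlation between a network's baseline and follow-up means is r = 0.820 × c. Covariate adjustment multiplies the treatment-effect variance by 1 − r².

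| c | r | Variance multiplied by | SE multiplied by |
|---|---|---|---|
| 0.7 | 0.574 | 0.670 | 0.819 |
| 0.8 | 0.656 | 0.569 | 0.754 |
| 0.9 | 0.738 | 0.455 | 0.674 |

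With no stratum effect in the simulation, the model without baseline had type I error of 0.051 and 0.057, so its standard error is valid.

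**4. What this does to power.** With 100 networks per arm, the effective size is 100 × 300 / 5.485 = 5,469 per arm.

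| True reduction | No adjustment | Strata only, R = 10–30% | Baseline only, c = 0.7–0.9 |
|---|---|---|---|
| 15% (20% vs 17%, planned) | 98.1% | 98.8–99.6% | 99.9% or more |
| 7.5% (20% vs 18.5%, assumed) | 51% | 55–63% | 68–84% |

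Power exceeds 80% in the first row because 2629 × 5.485 = 14,420 is the size of one arm. The 28,840 in the plan is the total for both arms, and the plan applies it to each. That is a separate point.

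**The case against.** The strongest reply is that the article is silent and does not exclude these terms. Its list of factors is introduced as examples, and a complete covariate list may stand in a full protocol or analysis plan that is not shown. Evaluating the outcome at baseline within multi-level models is also compatible with a model that uses baseline. This stands to the extent that one cannot say the trial will omit these terms. But the article does describe the model, its random effect and the kinds of adjustment. In doing so it passes over the one set of factors that its design calls prognostic and randomises on. Naming them is a better method than the one described.

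A second reply is that the size is uncertain. This stands too. R and c are assumed, R could be near zero, and the socioeconomic and hospital-sector adjusters may absorb part of what the strata explain.

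Three stronger readings are tempting and not supported.

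- A reader might infer that both omissions make the standard error wrong. Only omitting the strata does, and in the conservative direction.
- A reader might infer that all four time points go into one model with a single constant network effect, which could make the standard error too small and inflate type I error. The protocol commits to no such pooled model.
- A reader might take a far larger cluster size from the abstract's 1.9 million patients and the insurers' 41.49% coverage (1,900,000 × 0.4149 / 200 ≈ 3,940 per network) and so a larger effect. That assumes all those patients lie in the 200 randomised networks and that the coverage applies to them. The plan works with 300.

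**Conclusion.** The point holds as a recommendation to improve the stated model. As described, the model may give a standard error about 4–15% too large if the strata explain 10–30% of between-network variance. It also forgoes a variance reduction to about 67–45% if network effects correlate 0.7–0.9 over time. Both ranges rest on assumed inputs, with the plan's ICC of 0.015 and 300 patients per network.

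The treatment effect is not biased, and the false-positive rate is not raised. At the planned 15% reduction, power is about 98% with or without these terms. The practical gain comes if the effect is diluted. That is plausible, since meetings are voluntary, some were cancelled during the pandemic, and the analysis is by intention to treat. At half the planned effect, baseline adjustment would raise power from about 51% to between 68% and 84%.

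**What to change.** State that the primary multilevel model, at each follow-up time point, includes:

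1. region by urban/rural stratum as fixed effects, and
2. each network's pre-randomisation ACSH rate as a covariate,

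alongside the network random effect and the planned risk adjusters. Fix this before the outcome data are analysed, because the analysts will know the allocation and several risk-adjustment models are to be compared.

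The cost is wording only. Eight strata use at most 7 degrees of freedom among 200 networks, the baseline rate uses one more, and the baseline value is already planned from the routine data.
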